### Study population

For the purposes of the current study, we leverage the Northern Ireland Cohort for the Longitudinal Study of Ageing (NICOLA) and the NICOLA Harmonised Cognitive Assessment Protocol (HCAP) substudy (NICOLA-HCAP).^24^,^27^ NICOLA is a prospective representative cohort of over 8000 non-institutionalised individuals living across Northern Ireland, UK ≥50 years of age.^24 25^ Wave 1 of the NICOLA-HCAP study recruits a subsample of 1000 participants from NICOLA aged ≥65 years who previously took part in Wave 2 of NICOLA.^27^ The NICOLA-HCAP study is part of a framework for enhancing cross-national research within a group of ongoing studies worldwide, all of which are centred on the United States-based Health and Retirement (HRS) international family of longitudinal ageing cohort studies.^26 28^

The NICOLA-HCAP protocol consists of a battery of neuropsychological tests and is designed to provide detailed data on ability across a range of cognitive domains, including memory, executive function, language and visuospatial ability. The protocol was originally developed and implemented within HRS and has since been implemented in several other national ageing cohorts.^28^,^31^ The protocol is designed to be delivered in a harmonised way across studies to facilitate cross-national comparisons of dementia prevalence and risk factors. For the first wave of this study, we will recruit a sub-sample of participants from NICOLA-HCAP.

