### Confounders

Confounders such as age, sex, education, employment status, smoking, diet, cardiovascular risk factors, depression, years at home address will be accounted for.

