#### Total effect analysis

The focus of this analysis is the total effect of physical activity on cognitive function. The exposure variable will be operationalized as average daily MVPA minutes. We will assume that 7-day accelerometer measured physical activity represents the regular physical activity of a participant. The outcome variable will be operationalized as the MMSE score. We will use a directed acyclic graph (DAG) to identify our causal assumptions and a sufficient adjustment set according to d-separation rules.^50 51^ A preliminary DAG is provided in figure 4. We will employ the backdoor criterion for identification of the causal effect.^51^ This involves identifying potential confounding variables that could influence both the exposure and the outcome. Potential confounders include sociodemographic factors (age, sex, education, deprivation and marital status), capabilities (mobility, grip strength, sensory impairments) and opportunities (availability of greenspace and social relationships). By conditioning on these variables, we will be able to identify the total effect of physical activity (exposure) on cognitive function (outcome). Causes of the physical activity behaviour will be identified based on the COM-B model of behaviour.^52^ This will include physical (eg, physical or sensory impairments) and psychological capabilities (eg, previous cognitive function levels); physical (eg, access to recreation facilities) and social opportunities (eg, social support) of participants as well as sociodemographic characteristics. Multivariable linear regression models with doubly robust estimators will be used to estimate the average causal effect.^53^ As a sensitivity analysis, we will test various ways of operationalising the exposure and outcome. This will include average daily acceleration and average daily sedentary time for exposure, episodic memory and processing speed for outcome.

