#### Mediation analysis

Associations of environmental attributes (GIS data) with lifestyle behaviours and cognitive health will be estimated using multilevel modelling in a structural equation modelling framework,^54^ which is able to account for administrative unit-level and person-level (repeated measures) clustering and is appropriate for data with different distributions.^55^ Contemporary guidelines on discerning general from specific context effects will be followed.^56^ Plausible confounders will be identified using a pre-specified conceptual framework in conjunction with rules governing appropriate covariate selection and depending on the mechanism proposed, will be modelled as either a time-non-varying covariate, moderating or mediating effect as appropriate.^57^ Measurement of cognitive function took place in Waves 1+2 of NICOLA as well as the HCAP (in 2021), (26) yielding data that is amenable to use in a latent change score mediation within a multilevel SEM framework, satisfying the temporal ordering assumption for mediation analyses.^54 58 59^ Current guidelines on reporting SEM analyses will be followed.^60^ As a sensitivity check, an alternative approach to mediation from the causal inference literature will be used to decompose the total effect of the environment on cognitive function into direct, indirect and interactive effects.^61^ Based on a bias-corrected bootstrapping test of mediation, with 2000 bootstrap samples, and assuming a small (simulated at 0.14) effect size for both the path from environment to mediator and from mediator to environment, a sample size of approximately 462 would be required for a power of 0.8.^62^ Complementary to this, to further inspect putative causal relations between mediators and cognitive function, a 2-wave latent change score model (as previously used)^63^ will be used on a subset of Wave 1 NICOLA and NICOLA-HCAP respectively. Traditional bias-corrected bootstrapping will be used to determine whether lifestyle behaviours mediate the association between environmental exposures and cognitive outcomes. We will employ two strategies to mitigate collinearity, either: (1) composite measures of collinear variables or (2) the residual error term from preliminary bivariate regressions, will be included in multiple predictor models. Missingness will be assessed and, if missing at random or completely at random, will be addressed by full information maximum likelihood estimation for the mediation analyses.

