Multivariate analysis of variance will be conducted to investigate the difference in participant compositions (ie, part 1a and 2a) and the outcome of cognitive health. Compositional data analysis which is based on isometric log-ratio data transformation will then be conducted to model the association of time spent in different movement behaviours during waking hours and cognitive health.^64 65^ Minute-by-minute isotemporal substitutions will be made from one behaviour to another while holding the remaining behaviours constant, to model change in cognitive health. Adjustments for potential confounders and mediators will be made and includes age, sex, socioeconomic status, lifestyle behaviours (eg, smoking, drinking), disability, car ownership etc.

To control for multiple comparisons, the false discovery rate correction will be applied using the Benjamini-Hochberg procedure, adjusting for the total number of analyses conducted.

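### The compositional models do not name an earlier cognitive score as a covariate, although NICOLA scores should already be held and two of the questions concern decline

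*Protocol article*

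**What the plan says.** The Compositional data analysis section models cognitive health on the movement composition through isometric log-ratio (ilr) coordinates, followed by isotemporal substitutions. On covariates it says that adjustment, for confounders and mediators alike, "includes age, sex, socioeconomic status, lifestyle behaviours (eg, smoking, drinking), disability, car ownership etc". The general list reads: "Confounders such as age, sex, education, employment status, smoking, diet, cardiovascular risk factors, depression, years at home address will be accounted for". Neither names an earlier cognitive score.

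Other sections bear on this:

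- Total effect analysis lists causes of physical activity, among them "psychological capabilities (eg, previous cognitive function levels".
- Mediation analysis states: "Measurement of cognitive function took place in Waves 1+2 of NICOLA as well as the HCAP". It uses these repeated measurements in latent change score models.
- Study population says that NICOLA-HCAP recruits "participants from NICOLA aged ≥65 years who previously took part in Wave 2 of NICOLA", and the first wave of this study is drawn from NICOLA-HCAP.
- Questions 1b and 2b of the compositional analysis ask how the risk of cognitive decline alters when time is moved between behaviours. The text on the substitutions also speaks of change in cognitive health.
- Under Study procedure, the cognitive battery is completed first and the monitors are worn in the days that follow.

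**The concern.** Prior cognition plausibly drives both sides of the modelled relation. The plan itself gives it as a cause of physical activity, and it predicts current cognition. Under the backdoor reasoning that the plan adopts for the total effect, such a variable opens a confounding path between movement and cognition, and the compositional models estimate that same relation. If it is left out, the ilr coefficients and the substitutions can present a long-standing difference in ability as a consequence of how people spend their waking time.

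Two features sharpen this. At wave 1 the outcome is measured before the exposure, so reverse causation is a live possibility. And a single HCAP test score, with no earlier score in the model, shows level and not decline, so it cannot by itself answer 1b and 2b. The false discovery rate correction planned for these analyses does not remove confounding.

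**Working it through.** **The plan's own figure.** The article gives no power for the compositional models. Its only power statement is for the mediation test: N=462 for power 0.80 with both paths at 0.14. Simulating that test (bias-corrected bootstrap, 2000 resamples, no direct effect, two-sided 5%, 5000 simulated datasets) gives 0.801 at N=462, so the figure reproduces. At N=400 the same test has power 0.714.

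**Inputs for the compositional question**

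- n = 400 (Sample size section).
- Standardised slope b = 0.14, borrowed from the mediation paths.
- Two-sided 5%, before false discovery rate correction. The article states no alpha, so this is assumed.
- r = correlation of the earlier score with the HCAP outcome. Not in the article; assumed 0.3 to 0.6.
- q = correlation of the earlier score with the movement exposure. Not in the article; assumed 0.10 to 0.20.

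**A. Bias if the earlier score is omitted and there is no true effect.** The spurious standardised slope is r × q.

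- r = 0.5, q = 0.10: 0.5 × 0.10 = 0.05
- r = 0.5, q = 0.14: 0.5 × 0.14 = 0.07, half of the 0.14 effect
- r = 0.5, q = 0.20: 0.5 × 0.20 = 0.10

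For a spurious slope of 0.07, the expected z is 0.07 × √400 = 1.4, and Φ(1.4 − 1.96) = Φ(−0.56) ≈ 0.29. Simulation (4000 runs) gives 27.5%. For 0.10, z = 2.0 and Φ(0.04) ≈ 0.52; simulation gives 50.7%. With the earlier score in the model, the simulated rates are 5.1% and 5.0%. These runs treat the earlier score as measured without error; measurement error would leave part of the bias.

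**B. Precision if confounding is negligible (q = 0).** Power = Φ(b√(n/(1 − r²)) − 1.96).

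| r | b√(n/(1 − r²)) | Power | Gain (points) |
|---|---|---|---|
| score not used | 0.14 × 20 = 2.80 | 80.0% | – |
| 0.3 | 2.94 | 83.5% | about 4 |
| 0.4 | 3.06 | 86.3% | about 6 |
| 0.5 | 3.23 | 89.9% | about 10 |
| 0.6 | 3.50 | 93.8% | about 14 |

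If the other covariates already explain 10%, 20% or 30% of outcome variance, a partial correlation of 0.5 gains 8.7, 7.2 or 5.4 points. For joint tests with the same total effect at r = 0.5, power goes from 70.5% to 83.0% with 2 coordinates (part 1, three behaviours) and from 54.8% to 69.3% with 5 coordinates (part 2, six behaviours).

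**C. The two calculations do not add.** Take a true slope of 0.14 together with the confounding in A (0.07). The unadjusted slope is about 0.21, with z ≈ 0.21 × 20/√(1 − 0.21²) ≈ 4.3, and it is significant about 99% of the time. That is bias and not valid power, but no power is lost in that scenario. A applies where confounding is present, B where it is small.

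**The case against.** The strongest reply is that nothing is excluded. Both covariate lists are illustrative, the compositional one is open-ended, and an article may leave the complete set to an analysis plan. This stands against the stronger reading that a reader might infer, that the models will not adjust for earlier cognition: the documents support only that it is not named. It does not dispose of the point. The list is specific enough to include car ownership, yet it passes over a variable that the plan elsewhere treats as a cause of the exposure.

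A reader might also infer a fixed power loss of nine or ten points. The documents do not support that. It needs r of about 0.5, which is assumed, and an effect size taken from another analysis. Nor can it be claimed together with the false-positive rate, as step C shows.

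A third tempting reading is that the total-effect analysis commits to this adjustment, so that the two analyses conflict. It does not go that far. Previous cognition appears there as an example of a cause of activity, not in that section's list of potential confounders, and the graph that will settle the set is preliminary.

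Three further replies carry weight:

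- The outcome of the compositional models is not pinned down. If it is a change score, or an informant rating of decline such as the IQCODE, earlier cognition may already enter, and the figures above would not apply as they stand.
- If the recorded week reflects habitual activity, as the plan assumes for the total effect, past activity may have shaped the earlier score, and conditioning on it could remove part of the effect.
- Taking part in NICOLA Wave 2 does not guarantee a usable cognitive score.

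The first bears on how the fix is worded, the second is the reason to keep a model without the score, and the third calls for a rule on missing scores.

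**Conclusion.** The point holds as an omission from the named covariates. The plan gives earlier cognition as a cause of activity, should hold the scores for wave 1 participants, uses earlier scores in its mediation models, and asks about decline. Yet the compositional covariates do not name it. Confounding and reverse causation are the main ground, and precision is secondary.

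The sizes are illustrative. With no true effect, r = 0.5 and q = 0.14, the spurious slope is 0.07 with about 28% false positives. If confounding is small, power at n=400 for a slope of 0.14 rises from about 80% to 84–94% over r of 0.3 to 0.6, and by less once other covariates explain outcome variance. Both correlations are assumed, and 0.14 belongs to the mediation paths. The direction of the argument does not depend on these values; the sizes do.

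**What to change.** In the Compositional data analysis section, name two covariates for the part 1 and part 2 ilr models and the substitutions, at least for questions 1b and 2b: the NICOLA Wave 2 cognitive score (Wave 1 if Wave 2 is missing), and the time from that score to the HCAP visit. The score need not be on the HCAP scale to serve as a covariate. Where the outcome is defined as a change score, make sure that the earlier score is not left out of the model.

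Report the model without the earlier score as a sensitivity analysis, because earlier activity may have influenced that score. Participants with no earlier score, including any in the wave 2 refresh sample, enter that model only.

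The cost is a few sentences and one or two covariates from data that should already be held. The main model loses participants without an earlier score, and its estimate may be conservative for the effect of lifelong activity.

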### Patient and public involvement

To determine the acceptability and feasibility of this study we consulted with the NICOLA Healthy Ageing Research Advisory Group. This advisory group is made up of volunteers from AgeNI, a registered charity in Northern Ireland for older people and current NICOLA participants. Prior to commencing the study during the design and development phase the research team worked with members of the Advisory Group to obtain their feedback on a range of study elements. This included (but was not limited to): potential participant burden, monitor wear time, study procedures (eg, number participant phone calls, method of pack return) and future dissemination plans.

## Ethics and dissemination

###  Ethical approval

This study has been approved by the Queen’s University Belfast, Faculty of Medicine, Health, and Life Sciences Research Ethics Committee (MHLS 21_72). Prior to participation in the current study informed consent was obtained, with all participants completing and returning a written consent form.

### Data management

All researchers adhere to the Queen’s University Belfast quality assured process for data management, which follows the UK Economic and Social Research Council’s (ESRC) Research Data Policy. A Strategic Management Team (SMT) comprised of the experienced principal investigators and co-investigators, meets quarterly throughout this study. A monitoring schedule covering the roles and responsibilities of the researchers, the SMT for data quality, integrity, compliance, dissemination, safety, governance and ethics was developed and agreed. Data quality, follow-up and trial monitoring will be facilitated through a project specific database, including validation and compliance reports.

### Dissemination

This study protocol details an ongoing interdisciplinary research project that aims to examine the causal mechanisms between the urban environment and cognitive health, with a particular focus on the plausible pathways through physical activity, social activity and urban by-products in older adults in Northern Ireland. In addition, it has the potential to advance the methodological processes regarding the integration and analysis of accelerometry, GPS, GIS and cognitive health outcomes. Disseminating this work, which highlights the methodological approach for combining diverse datasets in a transparent and robust manner, allows future researchers to follow these methods to create and analyse granular temporospatial datasets using established methodologies. Regarding the findings from this study, they will be disseminated through peer-reviewed publications in high-ranking international journals, at national and international conferences and through the research teams far-reaching networks.
